## Type of analysis

The patients will be analyzed per protocol.

VARIABLES AND ENDPOINTS
Primary objective

The primary endpoint is the risk ratio between groups with and without rectus abdominis muscle atrophy for having parastomal hernia one year after surgery. The primary endpoint is derived from a modified Poisson regression model controlling for several covariates.

The variables associated with the primary objective are presence of rectus abdominis muscle atrophy <*varname_RAMatr>* and parastomal hernia at one year <*varname_Parastomal hernia>*.

Presence of rectus abdominis muscle atrophy will be determined by simultaneous retrospective examination by two radiologists of one-year CT examinations. Both assessors will examine the same image material, note their own judgment (rectus abdominis muscle atrophy yes/no) and then reach a consensus judgment. Cohen’s kappa will be reported as a measure of inter-rater agreement.

The determination of parastomal hernia at one year performed in the Stoma-Const trial will also be used in this study.

Further details are given in Table 1.

Secondary objectives

The secondary endpoints are the risk ratios between surgical techniques for developing RAM atrophy, and the risk ratio of a difference of stoma placement in RAM, measured from its medial limit, for developing parastomal hernia, respectively. The secondary endpoints are derived from modified Poisson regression models controlling for several covariates.

For the surgical techniques endpoint, the alternative technique of reinforcement of abdominal wall with a mesh around the stoma will be compared to the control techniques of cruciate incision and circular incision.

The variables associated with the secondary objectives are surgical technique <*varname_surgtec>* and presence of RAM atrophy <*varname_RAMatr>*, and stoma placement in RAM <*varname_stomaloc>* and parastomal hernia at one year <*varname_* parastomal hernia*>*, respectively.

Stoma placement in RAM will be determined by one radiologist assessor, measuring the distance from the medial RAM limit to the medial stoma border in mm.

Further details are given in Table 1.

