# STUDY METHODS

Data are drawn from the Stoma-Const study[[1](#_ENREF_1)], a prospective randomized study comparing the difference in risk for developing parastomal hernia one year after surgery with patients randomized to one of three surgical techniques:

- Cruciate incision (control)
- Circular incision
- Reinforcement of abdominal wall with a mesh around the stoma

The data material from StomaConst was deemed appropriate for use in a repeat retrospective analysis of rectus abdominis muscle atrophy and stoma placement in the rectus abdominis muscle.

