# ANALYSIS POPULATION, TYPE OF ANALYSIS

## Analysis population

The analysis population consists of all patients who were included in the original study for whom a one-year CT examination was performed at all Swedish centres.

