# STATISTICAL METHODOLOGY

## General principles

### Multiplicity

In accordance with study objectives, several comparisons will be made. To test the primary endpoint one risk ratio will be tested for significant difference from 1. To test the secondary endpoints, one comparison will be made for the endpoint concerning the effect of surgical technique on rectua abdominis muscle atrophy (mesh vs cruciate or circular incision) and one comparison will be made for the endpoint concerning the effect of stoma location on the parastomal hernia rate. We are aware of the risk for a type 2 error, but have chosen to perform the analyses with this knowledge and will interpret results with causion.

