### Interpretation of results

Due to randomization of surgical technique in the data material, any estimated effects of surgical technique on risk of rectus abdominis muscle atrophy can be interpreted causally.

Estimated effects of rectus abdominis muscle atrophy on risk of parastomal hernia and of stoma location on risk of rectus abdominis muscle atrophy cannot be interpreted causally. Instead, any such effects should be interpreted as correlational.

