## Sample size

The StomaConst study based its sample size on a power computation using a two-sided proportion test using normal approximation of the binomial distribution to obtain 80% power for a significance level of 0.05 and a true difference in proportion of 20%. This gave a sample size of 62 per group (three groups, one for each surgical technique).

For the present study, only patients for whom a one-year CT examination was performed at one of the Swedish centers are included, giving a sample size of 140. Approximating the incidence of rectus abdominis muscle atrophy as 37% for the mesh arm and 2% for the cruciate/circular arm (following Täckström 2022)[[2](#_ENREF_2)], 21 subjects are expected to display rectus abdominis muscle atrophy. Using the same test and significance level as above and assuming 44% incidence of parastomal hernia in the group without rectus abdominis muscle atrophy (following Correa Marinez 2020)[[1](#_ENREF_1)], this allows detection of a difference in proportion of 30% with 80% power for the primary endpoint.

For the secondary endpoint investigating risk ratio of surgical techniques for developing rectus abdominis muscle atrophy, the surgical technique arms consist of 88 subjects (cruciate/circular) and 52 subjects (mesh) respectively. Assuming rectus abdominis muscle atrophy incidence per arm as above, this gives >99.9% power.

Power for the secondary endpoint investigating risk ratio of stoma position for developing parastomal hernia is not easily computable in advance without knowledge of the distribution of stoma position in the sample. Thus, this power computation will be performed post-hoc.

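### The SAP calls the technique effect on atrophy causal because technique was randomised, but plans only a per-protocol analysis, which that reason does not cover

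*SAP*

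**What the plan says.** - **Type of analysis** (SAP, Analysis population, type of analysis): "The patients will be analyzed per protocol". The sentence covers all endpoints. The SAP does not define the term and plans no analysis by randomised arm. Its Additional analyses section lists none.
- **Study methods**: the source trial had "patients randomized to one of three surgical techniques" (cruciate, circular, mesh).
- **Multiplicity**: the one comparison for secondary objective 1 is "mesh vs cruciate or circular incision", with atrophy as the outcome.
- **Interpretation of results**: the causal reading opens with its reason, "Due to randomization of surgical technique in the data material", and concludes that "any estimated effects of surgical technique on risk of rectus abdominis muscle atrophy can be interpreted causally". It carries no qualification. The same section calls the other effects it lists correlational.
- **Analysis population**: "all patients who were included in the original study for whom a one-year CT examination was performed at all Swedish centres". Under Handling of missing values, incomplete records are removed listwise.
- **Sample size**: "only patients for whom a one-year CT examination was performed at one of the Swedish centers are included, giving a sample size of 140", split into 52 mesh and 88 cruciate/circular. The SAP does not say whether these counts follow allocation or technique received.
- **Covariates**: all models adjust for stoma aperture (fascia incision diameter from the perioperative form). They also adjust for stoma placement, which the Introduction says is measured on the one-year CT.

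**The concern.** Randomisation makes the groups comparable as they were allocated. A per-protocol analysis either drops patients who did not get the assigned technique or regroups patients by the technique used. Both steps depend on what happened after allocation, and if the reasons for deviating relate to atrophy, the groups are no longer comparable by design. A causal claim could still be argued from covariate adjustment and stated assumptions, but the SAP does not argue that. It appeals to randomisation alone.

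This is the one result that the SAP says may be read causally, so the manuscript would state it with more authority than the planned analysis earns. Three other features of the plan also separate the analysed comparison from the randomised one: selection on having a one-year CT, listwise deletion, and adjustment for two variables that arise during or after the operation.

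**Working it through.** **1. The sections side by side**

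| Step | SAP section | Fixed by randomisation? |
|---|---|---|
| Allocation to three techniques | Study methods | Yes |
| One-year CT at a Swedish centre | Analysis population | No, the CT comes a year after surgery |
| Per protocol | Type of analysis | No, depends on the technique carried out |
| Listwise deletion | Handling of missing values | No |
| Adjustment for aperture and placement | Covariates | No, both are features of the stoma as constructed |
| Causal reading because randomised | Interpretation of results | Needs groups as randomised |

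The last row relies on the first, but the steps between are not covered by it.

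**2. Reproducing the plan's figures**

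Inputs from Sample size: n = 88 and 52, atrophy 2% and 37%, two-sided 5% level, normal approximation.

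- Expected atrophy cases: 52 × 0.37 + 88 × 0.02 = 19.24 + 1.76 = 21.0, as stated.
- Power = Φ[(|p1 − p0| − 1.96 × SE0) / SE1], where SE0 uses the pooled proportion and SE1 the separate ones.
- Pooled proportion 21/140 = 0.15. SE0 = √[0.15 × 0.85 × (1/88 + 1/52)] = 0.0625. SE1 = √[0.02 × 0.98/88 + 0.37 × 0.63/52] = 0.0686.
- (0.35 − 1.96 × 0.0625)/0.0686 = 3.32, so power is 99.95%. This agrees with the stated >99.9%.

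The figures are sound. The problem is one of interpretation.

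**3. What analysis by randomised arm could cost**

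The SAP gives no crossover rate, so these rates are assumed. Let m be the share of the mesh arm without mesh and c the share of controls with mesh. Risk is assumed to follow the technique received, and 52/88 are taken as randomised counts:

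- p1 = 0.37(1 − m) + 0.02m
- p0 = 0.02(1 − c) + 0.37c

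| m | c | p1 | p0 | Expected risk ratio | Power |
|---|---|---|---|---|---|
| 0 | 0 | 37.0% | 2.0% | 18.5 | 99.95% |
| 10% | 0 | 33.5% | 2.0% | 16.8 | 99.8% |
| 20% | 0 | 30.0% | 2.0% | 15.0 | 99.5% |
| 30% | 0 | 26.5% | 2.0% | 13.3 | 98.5% |
| 0 | 5% | 37.0% | 3.75% | 9.9 | 99.8% |
| 0 | 10% | 37.0% | 5.5% | 6.7 | 99.5% |
| 20% | 10% | 30.0% | 5.5% | 5.5 | 96.6% |

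With a 2% control risk, the ratio is far more sensitive to controls receiving mesh than to mesh patients missing it. Power hardly moves. These are powers for the crude two-proportion test, as in the SAP, and not for the adjusted model. The table shows the dilution from analysing as randomised. It does not measure bias in the per-protocol estimate, which the SAP gives no means to compute.

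**The case against.** **Grouping by technique received is defensible for a tissue effect of mesh.** This stands as a reason to report such an analysis, and for the observational hernia models it may well be preferable. It does not make randomisation the ground for a causal reading of it.

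**The 140 may be unaffected.** A reader might infer that Analysis population and Type of analysis contradict each other on who is included, so that the 140 and the 52/88 split cannot stand. The documents do not support that. If per protocol means grouping by technique received, nobody is dropped, and 52/88 may already be counted that way. The definition may also stand in a protocol that is not at hand.

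**No deviation is documented.** Correct. The SAP reports neither a rate nor reasons, and some plausible reasons, such as BMI, are already covariates. The 52:88 split shows no imbalance either: an exact binomial test of 52 in 140 against one third, assuming equal allocation to three arms, gives p = 0.37.

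**Analysing as randomised does not by itself restore the causal claim.** This stands. CT availability, listwise deletion and the two post-randomisation covariates remain, so the remedy has to address them too. A minimal alternative is to leave the analysis as it is and withdraw the causal wording.

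**Conclusion.** The point holds in a limited form. The SAP's stated reason for a causal reading applies to groups as randomised, while the only analysis it plans is per protocol. The causal sentence is therefore unsupported as written.

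It would go too far to conclude that the estimate is biased. Without a deviation rate the bias cannot be sized, and it may be small. With an assumed 37% against 2%, none of the crossover rates examined brings the expected risk ratio below 5.5.

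Analysing as randomised is affordable. Power for the crude comparison stays above about 96% over the assumed ranges (up to 20% mesh-arm and 10% control crossover). The risk ratio itself could move noticeably toward 1.

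This should be fixed before analysis, but it is confined to secondary objective 1. The primary objective and the stoma-placement objective are observational and not affected by this point.

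**What to change.** 1. **Type of analysis.** Add for secondary objective 1: patients with a one-year CT are analysed in the technique group to which they were randomised. A per-protocol or as-treated analysis, with its definition written out, is a sensitivity analysis.
2. **Covariates.** For this model only, leave out stoma aperture and CT-measured stoma placement, since both arise after randomisation.
3. **Interpretation of results.** Limit the causal sentence to the as-randomised analysis. State that it is conditional on having a one-year CT at a Swedish centre and on complete data under listwise deletion.
4. **Sample size.** State whether 52 and 88 are counts by allocation or by technique received.

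The hernia models can keep technique received as the adjustment variable.

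The cost is a few sentences in the SAP, one sensitivity analysis and use of the allocation variable from the source trial. The statistical price is possible dilution: 18.5 to 9.9–6.7 if 5–10% of controls received mesh (assumed), with little loss of power. If the sponsor prefers to keep per protocol as the only analysis, the causal sentence should be reduced to an association.

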## Covariates, stratum and subgroups

Models for primary and secondary endpoints will be adjusted for potentially influential background variables by including as covariates the following variables:

1. Age
2. BMI
3. Sex
4. Method of surgery (laparoscopic/open surgery)
5. Comorbidity as defined in the Stoma-Const trial including diabetes and cardiovascular disease. Defined as yes or no to one of several co-morbidity questions (question 15 in preoperative questionnaire)
6. Stoma aperture area (from the perioperative CRF question 16, fascia incision diameter
7. Stoma placement in the rectus abdominis muscle (where it is not the endpoint variable) measured by one radiologist as the distance from the midline to the beginning (medial) of the stoma aperture

These covariates will be investigated for potential multicollinearity before modelling. If serious multicollinearity is detected, some variables may be excluded.

Further details are given in Table 1.

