# INTRODUCTION

This Statistical Analysis Plan (SAP) details the statistical and data related aspect of a planned manuscript on assessing whether rectus abominis muscle atrophy (*defined as a thinner muscle on the stoma side as seen on a postoperative computer tomography (CT) scan*) constitutes a protective factor for parastomal hernia (*defined as any herniation of intraabdominal content beyond the abdominal wall or a hernia sac identified in the prone or supine position on CT scan (if only the latter was available)*) as well as whether surgical technique used in colostomy construction constitutes a risk factor for rectus abdominis muscle atrophy and whether stoma placement (*measured from the medial limit of the muscle on 1-year CT scan)* constitutes a risk factor for parastomal hernia.

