### Type of analyses

The primary analyses for all endpoints will be adjusted analyses. Existence of serious multicollinearity as well as potential interaction effects between the explanatory variable and/or the covariates will be explored.

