### Dagitty code

dag {

bb="-4.843,-4.178,3.772,4.524"

"Mesh/No mesh" [pos="-0.125,-3.452"]

"Open/laparoscopy" [pos="-2.478,-2.181"]

"Rectus abdominis muscle atrophy" [exposure,pos="0.586,-0.093"]

"Stoma aperture" [pos="-4.125,0.439"]

"Stoma placement in the rectus abdominis muscle" [pos="-1.144,2.404"]

"parastomal hernia" [outcome,pos="-0.605,-0.502"]

Age [pos="2.074,-2.559"]

BMI [pos="1.634,2.119"]

Comorbidity [pos="3.054,0.088"]

Sex [pos="0.853,3.799"]

"Mesh/No mesh" -> "Rectus abdominis muscle atrophy"

"Mesh/No mesh" -> "parastomal hernia"

"Open/laparoscopy" -> "Rectus abdominis muscle atrophy"

"Open/laparoscopy" -> "parastomal hernia"

"Rectus abdominis muscle atrophy" -> "parastomal hernia"

"Stoma aperture" -> "parastomal hernia"

"Stoma placement in the rectus abdominis muscle" -> "Rectus abdominis muscle atrophy"

"Stoma placement in the rectus abdominis muscle" -> "parastomal hernia"

Age -> "Rectus abdominis muscle atrophy"

Age -> "parastomal hernia"

BMI -> "Stoma placement in the rectus abdominis muscle"

BMI -> "parastomal hernia"

BMI -> Comorbidity

Comorbidity -> "Rectus abdominis muscle atrophy"

Comorbidity -> "parastomal hernia"

Sex -> "Rectus abdominis muscle atrophy"

}

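### The technique-on-atrophy model adjusts for stoma aperture and one-year stoma placement, so its causal reading needs an assumption beyond randomisation that the SAP does not state

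*SAP*

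**What the plan says.** The section on covariates, stratum and subgroups sets one rule for every model: "Models for primary and secondary endpoints will be adjusted for potentially influential background variables by including as covariates the following variables". Seven items follow. Item 6 is "Stoma aperture area (from the perioperative CRF question 16, fascia incision diameter". Item 7 is "Stoma placement in the rectus abdominis muscle (where it is not the endpoint variable) measured by one radiologist". The exception in item 7 does not reach the technique model, whose endpoint is atrophy.

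The Introduction describes stoma placement as "measured from the medial limit of the muscle on 1-year CT scan". The methodology text on secondary endpoints takes the technique-on-atrophy model's other covariates from the common list. Under the heading on type of analyses, "The primary analyses for all endpoints will be adjusted analyses". The additional-analyses section plans nothing further. Items 6 and 7 are therefore in the only planned estimate of the technique effect.

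The section on interpretation of results then says, on the ground of randomisation, that "any estimated effects of surgical technique on risk of rectus abdominis muscle atrophy can be interpreted causally".

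**The concern.** Randomisation supports a causal reading of the technique contrast when it is unadjusted, or adjusted for variables settled before allocation. It does not by itself support a contrast conditioned on something measured during the operation or a year later. That needs a further assumption: that technique does not change the covariate, or, if only a direct effect is wanted, that nothing unmeasured drives both the covariate and atrophy. The SAP states neither and calls both variables background.

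Two things could go wrong. If technique shifts aperture or placement, and that variable alters atrophy risk, adjustment removes that part of the technique effect. If technique shifts the variable, and the variable shares an unmeasured cause with atrophy, adjustment also opens a non-causal path. Either way, the reported risk ratio would be presented as the effect of the randomised technique without being that quantity.

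**Working it through.** **1. The plan's own figures.** Inputs from the Sample size section: 52 mesh and 88 cruciate/circular patients, atrophy 37% and 2%, two-sided test at 0.05.

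- Expected cases: 52 × 0.37 + 88 × 0.02 = 19.24 + 1.76 = 21.0, as stated.
- Pooled risk 21/140 = 0.15. Null SE = √[0.15 × 0.85 × (1/88 + 1/52)] = 0.0625. Alternative SE = √[0.02 × 0.98/88 + 0.37 × 0.63/52] = 0.0686.
- Power = Φ[(0.35 − 1.96 × 0.0625)/0.0686] = Φ(3.32) = 99.95%. With unpooled variance it is 99.92%. The stated power above 99.9% reproduces and is not disputed. It was computed for the unadjusted contrast.
- Planning risk ratio: 0.37/0.02 = 18.5. SE of its log = √[0.63/19.24 + 0.98/1.76] = 0.768, so the approximate 95% CI is 4.1 to 83.

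**2. When the two variables arise.** Aperture is the fascia incision diameter on the perioperative form, so it is part of the operation. Placement is read on the one-year CT according to the Introduction; item 7 does not name the scan, and I assume it is the same measurement. Atrophy is also judged on the one-year CT. The SAP does not say when randomisation or choice of stoma site took place. That aperture follows allocation is a safe inference; for placement, only the time of reading is known.

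**3. What the plan's causal graph implies.** The graph under Dagitty code was drawn with atrophy as exposure and hernia as outcome. Read for technique on atrophy:

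- No arrow enters the mesh node, so no adjustment is needed for confounding.
- Arrows leave the mesh node only to atrophy and to hernia. None goes to aperture or placement.
- Aperture has one arrow, to hernia, and none to atrophy.
- Placement has an arrow to atrophy and one to hernia.

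If the graph is right, adjusting for both items leaves the technique risk ratio unbiased, and placement could at most add precision. If an arrow from mesh to either item is missing, adjustment can bias it.

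**4. Size, under assumed values only.** Let mesh shift a standardised covariate by s SD, and let that covariate multiply atrophy risk by exp(b) per SD. Under a log-linear model without interaction or an unmeasured common cause, adjusted RR = 18.5 × exp(−s·b). The last column is a Poisson-regression simulation with 400,000 patients, marginal risks held at 2% and 37%, and individual risks capped at 1.

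| s (SD) | b | 18.5 × exp(−s·b) | Simulated adjusted RR |
|---|---|---|---|
| 0 | 0.4 | 18.5 | 18.5 |
| 0.25 | 0.2 | 17.6 | 17.3 |
| 0.5 | 0.2 | 16.7 | 16.8 |
| 0.5 | 0.4 | 15.1 | 15.1 |
| 1.0 | 0.2 | 15.1 | 15.0 |
| 1.0 | 0.4 | 12.4 | 12.6 |

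In these rows the simulated unadjusted RR ran from 18.2 to 18.7, so differences of a few tenths are noise. The sign is open as well: s = −0.5 with b = 0.4 gives 18.5 × exp(0.2) = 22.6, and s = −1 gives 18.5 × exp(0.4) = 27.6.

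**5. Adding an unmeasured common cause.** Let such a factor correlate 0.5 with the covariate (at no shift) and have a log RR of 0.3 on atrophy. With s = 1 and b = 0.4 the simulated adjusted RR is 11.0, against a true direct RR of 12.4 and a total RR of 18.5. With s = 1 and b = 0 it is 15.8, although the direct and total RR are both 18.5. With s = 0, adjusted and unadjusted estimates agree to within 0.1.

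**The case against.** The strongest reply is that the plan's own graph shows no problem. It draws no effect of mesh on aperture or placement, and the risk ratio is collapsible, so on that graph adjustment does no harm. Placement is drawn as a cause of atrophy, and adjusting for an outcome cause that treatment does not affect is ordinary practice. That stands, and it is why the point is conditional.

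Three stronger readings are tempting and are not supported.

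- A reader might infer that technique partly sets both variables. No section says so. It is plausible for aperture, because two of the three arms under Study methods are defined by type of incision. But the third arm is a mesh reinforcement, and the tested contrast pools the two incision arms. For placement, a one-year reading does not show that technique moved the stoma.
- A reader might infer that the model estimates a controlled direct effect. That needs no unmeasured common cause of covariate and atrophy and no technique-by-covariate interaction. Without these, the estimate may be neither the total effect nor a controlled direct effect.
- A reader might infer that the causal sentence is wrong. It is incomplete: it holds under an assumption that the SAP leaves unstated.

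It can also be said that an effect near the planning value would remain very large in every case in the working. That is so, and it limits the severity. It does not make the estimate the quantity that the SAP says it is.

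**Conclusion.** The point holds conditionally. The SAP puts an intra-operative and a one-year measurement into its only planned technique-on-atrophy estimate, labels them background, and rests a causal reading on randomisation alone. If technique affects neither variable, there is no bias. If it affects one, and that variable is related to atrophy or shares an unmeasured cause with it, the adjusted risk ratio is not the total effect of the randomised technique.

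Size and direction cannot be derived from the documents. The range from no change to about 12.6, against 18.5, rests on assumed shifts of 0 to 1 SD and at most exp(0.4) per SD; an unmeasured common cause can move it further, and an opposite shift raises it. The stated power is unaffected.

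This should be fixed but does not undermine the plan: the endpoint is secondary. The per-protocol analysis and the restriction to patients with a one-year CT limit the causal claim separately, and removing two covariates does not lift those limits.

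**What to change.** In the covariates section, state that items 6 and 7 are not used in the technique-on-atrophy model, and that its primary estimate uses only variables settled before randomisation, or none. Age, BMI, sex and comorbidity fit that description. The SAP should say whether item 4 means the approach planned before allocation or the one performed. Keep aperture and placement in the hernia models, where the graph gives both an arrow to the outcome; placement is the exposure in its own model. Report any technique model that contains them as supplementary and non-causal. If the authors prefer to keep the adjustment in the primary estimate, the interpretation section must state the assumption that technique affects neither variable.

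The cost is a sentence or two and a shorter formula: technique plus seven covariates is 8 slopes, and without the two items it is 6, for 21 expected cases. Under the listwise-deletion rule, a missing aperture or placement value would also no longer remove a patient from this comparison, where only 88 × 0.02 = 1.76 cases are expected in the cruciate/circular group. The downside is a possible small loss of precision from dropping placement, which the graph shows as a cause of atrophy.
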